**Table 3: Dose delay and adjustment due to hepatic function abnormal**

| Toxicity / NCI-CTCAE grade                                                                                                                                                                                                                                                                                                                                                                                                                                                                                                                                                                                                            | Actions to be taken                                                                                                                                                                                                                                                                                                                                                                                                                                                                                                                                                                                                                            |
|---------------------------------------------------------------------------------------------------------------------------------------------------------------------------------------------------------------------------------------------------------------------------------------------------------------------------------------------------------------------------------------------------------------------------------------------------------------------------------------------------------------------------------------------------------------------------------------------------------------------------------------|------------------------------------------------------------------------------------------------------------------------------------------------------------------------------------------------------------------------------------------------------------------------------------------------------------------------------------------------------------------------------------------------------------------------------------------------------------------------------------------------------------------------------------------------------------------------------------------------------------------------------------------------|
| Total bilirubin increased (without ALT/AST increased)                                                                                                                                                                                                                                                                                                                                                                                                                                                                                                                                                                          |                                                                                                                                                                                                                                                                                                                                                                                                                                                                                                                                                                                                                                                |
| Grade 1                                                                                                                                                                                                                                                                                                                                                                                                                                                                                                                                                                                                                               | 
 
1. Monitor liver function once a week.
 
2. No dose adjustment is required.
 
                                                                                                                                                                                                                                                                                                                                                                                                                                                                                                           |
| Grade 2: Total bilirubin $> 1.5 \times \text{ULN}$ and $\leq 3 \times \text{ULN}$                                                                                                                                                                                                                                                                                                                                                                                                                                                                                                                                                     | 
 
1. Increase the frequency of liver function monitoring (once every 2-3 days) until it recovers to baseline level.
 
2. Dose adjustment: 
 
a) If toxicity resolves to Grade <math>\leq 1</math> within 14 days (inclusive), resume HQP1351 administration at the original dose level.
 
b) If toxicity resolves to Grade <math>\leq 1</math> beyond 14 days, or toxicity recurs, resume HQP1351 administration at a reduced dose level.
 
c) If toxicity recurs after two dose reductions, stop HQP1351 administration.
 
 
 
 |
| Grade 3: Total bilirubin $> 3 \times \text{ULN}$ - $10.0 \times \text{ULN}$                                                                                                                                                                                                                                                                                                                                                                                                                                                                                                                                                           | 
 
1. Increase the frequency of liver function monitoring (once every 2-3 days) until it recovers to baseline level.
 
2. Dose adjustment: 
 
a) If toxicity resolves to Grade <math>\leq 1</math> within 14 days (inclusive), resume HQP1351 administration at a reduced dose level.
 
b) If toxicity resolves to Grade <math>\leq 1</math> beyond 14 days, or toxicity recurs, stop HQP1351 administration.
 
 
 
                                                                                                                     |
| Grade 4: Total bilirubin $> 10.0 \text{ ULN}$                                                                                                                                                                                                                                                                                                                                                                                                                                                                                                                                                                                         | Stop HQP1351 administration.                                                                                                                                                                                                                                                                                                                                                                                                                                                                                                                                                                                                                   |
| Confounding variables and/or other causes of total bilirubin increased should be excluded before dose interruption/reduction. They include, but are not limited to, evidence of obstruction (e.g., typical ALP and GGT increased due to gallbladder or bile duct disease), hyperbilirubinemia (i.e., direct bilirubin $\leq 1 \times \text{ULN}$ ) due to indirect bilirubin increased as a result of hemolysis or Gilbert syndrome, drug treatment, viral hepatitis, alcoholic or autoimmune hepatitis, and hepatotoxic drugs. For patients with Gilbert syndrome, these dose adjustments apply only to changes in direct bilirubin. |                                                                                                                                                                                                                                                                                                                                                                                                                                                                                                                                                                                                                                                |
| AST/ALT increased (without <math>> 2 \times \text{ULN}</math> total bilirubin increased)                                                                                                                                                                                                                                                                                                                                                                                                                                                                                                                                    |                                                                                                                                                                                                                                                                                                                                                                                                                                                                                                                                                                                                                                                |
| Consistent with baseline grade, or increase from baseline Grade 0 to Grade 1                                                                                                                                                                                                                                                                                                                                                                                                                                                                                                                                                          | 
 
1. Monitor liver function once every 2 weeks.
 
2. No dose adjustment is required.
 
                                                                                                                                                                                                                                                                                                                                                                                                                                                                                                    |
| Grade 2 ( $>3.0$ - $5.0 \times \text{ULN}$ )                                                                                                                                                                                                                                                                                                                                                                                                                                                                                                                                                                                          | 
 
1. Increase the frequency of liver function monitoring (once every 2-3 days) until it recovers to baseline level.
 
                                                                                                                                                                                                                                                                                                                                                                                                                                                                            |

[figure not shown]

| Toxicity / NCI-CTCAE grade                                                                                                                                                                                                                                                                                                                                                                                                                                                                                             | Actions to be taken                                                                                                                                                                                                                                                                                                                                                                                                                     |
|------------------------------------------------------------------------------------------------------------------------------------------------------------------------------------------------------------------------------------------------------------------------------------------------------------------------------------------------------------------------------------------------------------------------------------------------------------------------------------------------------------------------|-----------------------------------------------------------------------------------------------------------------------------------------------------------------------------------------------------------------------------------------------------------------------------------------------------------------------------------------------------------------------------------------------------------------------------------------|
|                                                                                                                                                                                                                                                                                                                                                                                                                                                                                                                        | 2. Dose adjustment:
a) If toxicity resolves to Grade $\leq 1$ within 14 days (inclusive), resume HQP1351 administration at the original dose level.
b) If toxicity resolves to Grade $\leq 1$ beyond 14 days, or toxicity recurs, resume HQP1351 administration at a reduced dose level.
c) Stop HQP1351 administration if toxicity recurs after two dose reductions or if toxicity resolves to baseline level beyond 14 days. |
| Grade 3 ( $>5.0 - 20.0 \times \text{ULN}$ )                                                                                                                                                                                                                                                                                                                                                                                                                                                                            | 1. Increase the frequency of liver function monitoring (once every 2-3 days) until it recovers to baseline level.
2. Dose adjustment:
a) If toxicity resolves to $\leq$ baseline level within 14 days (inclusive), resume HQP1351 administration at a reduced dose level.
b) Stop HQP1351 administration if toxicity resolves to $\leq$ baseline beyond 14 days or toxicity recurs.                                            |
| Grade 4 ( $>20 \times \text{ULN}$ )                                                                                                                                                                                                                                                                                                                                                                                                                                                                                    | Stop HQP1351 administration.                                                                                                                                                                                                                                                                                                                                                                                                            |
| AST/ALT increased with total bilirubin increased                                                                                                                                                                                                                                                                                                                                                                                                                                                                |                                                                                                                                                                                                                                                                                                                                                                                                                                         |
| For patients with normal ALT, AST, and total bilirubin levels at baseline: AST or ALT $> 3.0 \times \text{ULN}$ , and total bilirubin $> 2 \times \text{ULN}$ , no evidence of cholestasis
or
For patients with AST or ALT or total bilirubin increased at baseline: baseline [AST or ALT $> 2 \times \text{baseline}$ and $> 3.0 \times \text{ULN}$ ] or [AST or ALT $8.0 \times \text{ULN}$ ], whichever is lower, combined with [total bilirubin $> 2 \times \text{baseline}$ and $> 2.0 \times \text{ULN}$ ] | 1. Stop HQP1351 administration.                                                                                                                                                                                                                                                                                                                                                                                                         |

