### **4.3 Dose Delay and/or Dose Reduction**

#### **4.3.1 Dose interruption**

Treatment may be interrupted for up to 2 weeks (14 days) to allow study drug-related toxicity to recover to baseline or Grade  $\leq 1$ . For non-treatment-related or unexpected toxicity, whether to discontinue treatment should be decided after discussion between the investigator and the sponsor. If HQP1351 is discontinued for more than 2 weeks (14 days), the subject will be withdrawn from the study. The subject can stay in the study to receive low-dose HQP1351 treatment (determined upon discussion by the principal investigator and the sponsor) if it is considered that the subject can benefit from continuous study treatment.

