#### **4.3.2 Dose adjustment**

AEs that occur during this study will be graded according to National Cancer Institute-Common Terminology Criteria for Adverse Events (NCI-CTCAE) (v4.03). According to the correlation of AEs with the study drug and grade, the investigator will take different actions with the study drug, including maintaining the original treatment regimen, withholding dosing, reducing the dose, and terminating the treatment. Up to twice dose reductions are allowed, each to the next lower dose already explored. Any adult subject requiring a reduction of HQP1351 dose below 30 mg QOD should permanently discontinue the study treatment. The study drug can be resumed when the study drug-related toxicities resolve to grade 1 or below.

Dose adjustment may not be performed for grade 1/2 toxicities related to the study drug that can be treated by supportive treatment or don't influence normal daily activities of subjects, unless QTc prolongation, clinically significant pancreatitis, or other clinical conditions that affect subject's safety at the investigator's discretion. For intolerable (symptomatic or influencing subject's normal daily activities) or persistent (unable to be handled with the best supportive care and recovered to grade 1 or baseline after up to 2-week of drug withdrawal) grade 1/2 toxicities related to the investigational product, whether to make dose adjustment will be determined by discussion between the PI and the sponsor.

If a subject experiences grade 3 or 4 investigational drug-related toxicities, the investigational drug should be interrupted immediately. A maximum of 2 weeks (14 days) of drug interruption is permitted to resolve toxicities to Grade 1 or below, or baseline level. The investigational drug can be resumed when the toxicities resolve to Grade 1 or below, or baseline level. Each subject may undergo a maximum of twice dose reductions throughout the study period, and dose increases are generally no longer allowed after dose reductions. Please refer to Table 2-4 for guidance on dose adjustment for study drug-related toxicity.

[figure not shown]**Table 2: Dose delay and adjustment due to hematologic toxicities**

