### **9.2.6 Correlation between an AE and the study drug**

Investigators should evaluate the causal relationship of each case of AE to the study drug based on medical and scientific judgment with reference to the following criteria:

- (1) Related: occurrence of the event has reasonable temporal relationship with administration, and the event is consistent with known property of the investigational drug, which is improved after dose reduction or interruption and recurs after re-administration and the subject's clinical condition or other treatments can not explain the event.
- (2) Possibly related: occurrence of the event has reasonable temporal relationship with administration, the event is consistent with known property of study drug, and the subject's clinical condition or other treatment may also cause the event.
- (3) Unlikely related: the temporal relationship between the occurrence of the event and administration is uncertain, and the event is not likely to be consistent with known property of the study drug, and the subject's clinical condition or other treatment may also cause the event.
- (4) Not related: occurrence of the event has no reasonable temporal relationship with administration, the event is not consistent with known property of the study drug, and the subject's clinical condition or other treatment may also cause the event. The event lessens or disappears when the disease condition is improved or other treatment is discontinued.

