##### **10.4.3 Safety data**

All AEs will be coded according to Medical Dictionary for Regulatory Activities (MedDRA). The frequency (number and percentage of subjects) of subjects experiencing one or more AEs will be calculated and summarized by System Organ Class (SOC) and Preferred Term (PT). All AEs, drug-related AEs (AEs assessed as related or possibly related), AEs and SAEs graded based on NCI CTCAE, and AEs resulting in study withdrawal will be classified and summarized.

AEs and outliers (patient's physical examination results, vital signs, and laboratory results) determined by the investigator to be clinically significant will be summarized and tabulated by dose group.

Deaths, SAEs, and AEs leading to discontinuation of HQP1351 treatment will be listed in detail.

[figure not shown]

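### For an isolated Grade 3 bilirubin rise judged possibly related, Section 4.3.2 says to hold HQP1351 at once, but the Table 3 note puts the work-up for other causes before the hold

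*Protocol*

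**What the plan says.** Protocol Section 4.3.2 gives the general rule: "If a subject experiences grade 3 or 4 investigational drug-related toxicities, the investigational drug should be interrupted immediately". It then refers to Tables 2 to 4 for guidance on toxicity related to the study drug. It does not say which prevails if the text and a table differ.

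In Table 3, the Grade 3 row for total bilirubin without raised ALT/AST covers values above 3 and up to 10 times ULN. Its first step is "Increase the frequency of liver function monitoring (once every 2-3 days) until it recovers to baseline level". Its second step covers only what follows a hold: on recovery to Grade 1 or below "within 14 days (inclusive), resume HQP1351 administration at a reduced dose level", and otherwise stop. A note closes the bilirubin rows: "Confounding variables and/or other causes of total bilirubin increased should be excluded before dose interruption/reduction". The causes it lists include biliary obstruction, hemolysis, Gilbert syndrome, several forms of hepatitis and hepatotoxic drugs. Its one special case is "For patients with Gilbert syndrome, these dose adjustments apply only to changes in direct bilirubin".

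Two other sections bear on the reading. Section 9.2.6 describes a possibly related event as one where "the event is consistent with known property of study drug, and the subject's clinical condition or other treatment may also cause the event". Section 10.4.3 tabulates "drug-related AEs (AEs assessed as related or possibly related". For toxicity that is not treatment-related, Section 4.3.1 has a separate route: "For non-treatment-related or unexpected toxicity, whether to discontinue treatment should be decided after discussion between the investigator and the sponsor".

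**The concern.** An investigator who sees an isolated bilirubin of, say, 5 times ULN and judges it possibly related finds two instructions. The main text says to hold now. The note says to exclude other causes first, and the row gives no start for the hold that would settle the order. Read literally, the note lets every-other-day dosing continue above 3 times ULN for as long as the work-up takes.

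Two sites could therefore act differently on the same result, in a trial whose primary endpoint is safety and tolerability. What is at stake is subject protection and uniform dosing. Sample size, error rates and the efficacy analyses are not touched.

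**Working it through.** The plan states no figure to reproduce. The check is a comparison of text, plus two small counts for scale.

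**1. Which events fall under both instructions?** Go through the categories of Section 9.2.6 for an isolated Grade 3 rise.

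| Judgement | Section 4.3.2 | Table 3 note | Conflict? |
|---|---|---|---|
| Related | Hold at once | Already met: this category requires that the subject's condition and other treatment cannot explain the event | No |
| Possibly related | Hold at once, if drug-related includes this category | Not met: another cause is still open | Yes |
| Unlikely or not related | Not covered; 4.3.1 discussion applies | Consistent with 4.3.1 | No |

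Other cases also drop out:
- Grade 2: the immediate rule covers Grades 3 and 4 only.
- Grade 4: the row says to stop, and the note speaks only of interruption or reduction.
- Combined AST/ALT and bilirubin rises: the row says to stop.
- Gilbert syndrome without a rise in direct bilirubin: the note excludes it from the adjustments.

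**2. Does the row supply the order?** No. To resume presupposes a hold, but no step starts one. In Table 2, the Grade 3 rows for platelets, neutrophils, febrile neutropenia and anemia all open with an interruption step. The Grade 3 AST/ALT row also lacks one, but no note there postpones the hold. The bilirubin block alone has both gaps.

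**3. Is the case realistic?** Section 1.5.2 names blood bilirubin increase within the common liver-test abnormalities of the CML studies, so a rise can fit a known property of the drug. The eligibility criteria allow for liver metastasis, so a competing cause is plausible. Possibly related is then a natural judgement.

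**4. Extra dosing, as an illustration.** The protocol does not state how long the work-up takes. Assume it lasts one retest interval of the Grade 3 row (2 to 3 days). The number of every-other-day doses falling in k days lies between floor(k/2) and ceil(k/2).

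- k = 2: 1 dose.
- k = 3: 1 to 2 doses.
- So 1 to 2 doses in 2 to 3 days: 30 to 60 mg at 30 mg QOD, 40 to 80 mg at 40 mg QOD, 50 to 100 mg at 50 mg QOD.
- Under 4.3.2: 0 doses.

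**5. How many subjects?** Section 1.5.2 lists the non-hematological events seen in at least 20% of the 36 GIST subjects, and a bilirubin increase is not among them. If that list is complete, at most 7 subjects had one of any grade: 7/36 = 19.4%, whereas 8/36 = 22.2% would have been listed. Isolated, possibly related Grade 3 rises would be fewer.

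**The case against.** The strongest reply is that causality comes first by design. Section 4.3.2 says the action taken depends on the event's relation to the drug and on its grade, and its immediate rule covers drug-related toxicity only. On this reading the note is the causality step for bilirubin: check the listed causes, then hold at once if the drug is to blame. This stands for related events. It does not settle possibly related ones, where the investigator has made the causality judgement and another cause remains open.

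A second reply is that Section 10.4.3 defines drug-related for tabulation, not dosing. Elsewhere, when the protocol wants both categories in a clinical rule, it names both, as in the criterion for moving 3+3 subjects to a higher dose (Section 4.1). That is fair. Carrying the 10.4.3 meaning into 4.3.2 is an inference, though a natural one, since 10.4.3 uses the same term. Both the rule and the note say should, so neither outranks the other on wording.

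A reader might infer more than the documents support in three ways:
- That the whole 14-day window could pass on drug. The 14 days limit recovery and time off drug; they say nothing about the work-up.
- That the work-up cannot be done because the scheduled chemistry panel lists neither GGT nor direct bilirubin, although the note relies on both. Section 7 provides for unscheduled examinations when clinically indicated, so the panel does not prevent it.
- That checking for other causes is itself wrong. With liver metastasis allowed, it is sensible. Only its place before the hold is at issue.

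**Conclusion.** The point holds as a minor safety conflict, confined to an isolated Grade 3 total bilirubin rise judged possibly related to HQP1351. There, 4.3.2 calls for a hold at once, the Table 3 note asks for the work-up first without a time limit, and the Grade 3 row does not say when the hold starts.

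The conclusion assumes that drug-related in 4.3.2 includes possibly related. If the sponsor meant related only, the conflict disappears, but the protocol should then say so. The dose count is conditional on an assumed 2 to 3 day delay, because the true work-up time is not given. Few subjects are likely to be affected, and no liver harm is quantified.

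**What to change.** Add as step 1 of the Grade 3 bilirubin row: *Interrupt HQP1351 immediately if the event is judged related or possibly related (in Gilbert syndrome, based on direct bilirubin only).*

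Reword the note for this grade: *For Grade 3, other causes are investigated during the interruption. If another cause is confirmed and the event is reclassified as unlikely or not related, restart and dose level are decided by the investigator and sponsor (4.3.1), and the Grade 3 dose reduction and the 14-day withdrawal rule do not apply. If no other cause is confirmed, the event is handled as drug-related under steps 2a/2b.*

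Two variants should be avoided. Requiring other causes to be excluded before dose reduction would move the same conflict to step 2a, since they may remain open in a possibly related event. Making restart wait for bilirubin recovery after a confirmed unrelated cause, with the 14-day limit unchanged, could lead to withdrawal of that subject under 4.3.1.

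The cost is one added step and a reworded note at the next amendment, with no extra subjects or scheduled visits. The downside is missed doses in subjects whose rise proves unrelated: 1 to 2 doses for each 2 to 3 days of hold.
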